### ***7.3. Request for exemption from the collection of consent***

The PrevHPV study is an interventional research in the field of public health, that is to say it is aimed at target populations (all adolescents attending middle school in the 90 participating municipalities and their parents) and not individuals specifically designated. The population-based nature of this research is difficult to reconcile with the collection of individual consent as requested by article L. 1122-1-1 of the Public Health Code. As a result, the CPP will be asked to be able not to collect individual consent from populations to participate in research, in accordance with article L. 1122-1-4 of the Public Health Code.

However, a letter (accompanied by an information note adapted according to the assigned group) will be sent to the families of all adolescents attending participating establishments via the schools in order to present the research to them.

#### **7.4. Evaluation of the effect on knowledge, attitudes, beliefs and practices**

The repeated cross-sectional survey (before - after) KABP-6C is carried out in the following populations:

- Adolescents (girls and boys), enrolled in Grades 8 & 9 classes in middle schools (public and private) located in the 90 participating municipalities.
- Parents of adolescents (girls and boys), enrolled in middle schools (public and private) located in the 90 participating municipalities.
- GPs practicing in municipalities in groups 1, 2, 5 and 6.

(i) KABP-6C survey among middle school students and their parents:

With authorization from the principals/directors of each middle school, the information and the invitation to the survey will be communicated to families through the middle school's usual means of communication. Parents may object to their child's participation. The T0 (before) and T1 (after intervention) questionnaires, self-administered and online, will be accessible via a specific research internet link.

The adolescent questionnaires will be administered in class under the supervision of a teacher or health professional. Each participant will be assigned an inclusion number, determined in advance by the middle school referent, to be entered in the T0 and T1 questionnaires which will make it possible to establish the link between the pre- and post-intervention questionnaires (T0 and T1). During the T0 survey, students will be asked to note this number in their correspondence notebook. A list of inclusion numbers and student names will be established for each class. All lists of the different classes will be kept in a closed envelope in the locked office of the research referent in the establishment, until they are transferred to the classes at T1. On this occasion, school staff present in class for the T1 questionnaire will be able to remind students of their inclusion number.

Parents will receive a survey invitation with the link to the research site. They will complete the T0 and T1 questionnaires at home, without the presence of children. Parents will be asked to enter their child's inclusion number (given in class and noted in the correspondence book), in order to be able to establish the family link while remaining anonymous. Parents will also be asked to note this inclusion number and keep it until the T1 survey.

The correspondence between inclusion number (which will make it possible to establish the link between T0 and T1, and between children and parents) and the identity of the participants will only be documented in the students' individual correspondence notebook and on the list kept for each class by the middle school's research referent. These lists will be destroyed after the questionnaires are administered to T1 in each class. Investigators will not have access to these lists.

(ii) KABP-6C survey among GPs:

For each of the municipalities in groups 1, 2, 5, and 6 the list of GPs practicing within each of them is established. These GPs are then contacted by telephone to ask them to participate in the KABP-6C survey. Each participant will be assigned an inclusion number which will make it possible to establish the link between the pre- and post-intervention questionnaires (T0 and T1).

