### **7.2. Inclusion, information, and participation agreement**

The selection process, information - participation agreement, and inclusion is as follows (see paragraph 5.3 Selection methods):

- Identification of eligible academies,
- Information from the rectorates of eligible academies and diocesan directorates of eligible departments by mail (DGESCO director letter + PrevHPV's SC letter),
- Identification of 409 eligible municipalities in eligible academies,
- Information by mail then telephone from the principals and directors of the middle schools of the 409 municipalities + request for participation agreement (→ identification of the 90 participating municipalities),
- Randomization of the allocation group (group 1 to 6) of the components for each participating municipality,
- Information for principals and directors of each middle school in their assigned group,
- Information for the mayors of each of the 90 participating municipalities and the corresponding

departmental councils,

- Information for GPs in municipalities in groups 1, 2 and 5, verification of eligibility and agreement to participate in training.

For each middle school of the 60 municipalities randomized to groups 1, 2, 3 and 4 (benefiting from EMM alone or EMM + facilitation of access to vaccination), the principal/director is in charge of informing the staff (health, teaching, administrative) of his middle school of the component they will receive. It will be essential that a referent be appointed within each middle school (school nurse/doctor, biology teacher, administrator, etc.) to be the main contact for the PrevHPV SC and to act as a link between the research teams and the actors in the field of experimentation.

Students and parents (or legal guardians) of each middle school in the 60 municipalities are informed by a letter at the end of 2020 by the referent and the principal/director of the component(s) (EMM or EMM + facilitation of access to the vaccination) deployed in their middle school between January and May 2021.

For the middle schools of the 30 municipalities randomized to groups 1 and 3 (benefiting from the 'Facilitation of access to vaccination' component), an information letter and collection of consent to vaccination are sent by the referent and/or each principal/school director, in January/February 2021, to the parental authority of each student enrolled in the school to propose the initiation of HPV vaccination at their child's school.

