- (ii) Educational videos of 10 to 12 minutes covering 4 themes: pathologies linked to HPV, risk of being infected by HPV, barriers to vaccination, advantages of being vaccinated. These videos will be constructed by health students during the co-construction phase, and will be the subject of a competition to select the best videos. They will be accompanied by explanatory sheets. The jury for this competition will be made up of the project steering committee: 3 videos will be selected. The call for competition will be distributed by the University College of Public Health Teachers, and Health student associations.
- (iii) Educational tools and training intended for biology teachers and school nurses, including existing materials and materials created during the co-construction phase as part of the research (development of an interactive course that they can use with students).

This component also includes information meetings for parents who can come with their teenagers if they wish. These information meetings will be led by GPs, infectious disease specialists and/or gynecologists. Educational support will be co-created by the PrevHPV SC and can be used by speakers at these information meetings. In this context and when possible, we will call on health students integrated into the SeSa systems, particularly for interventions with students.

The implementation of the EMM component with adolescents and their parents will take place on the middle school site between 01/01 and 03/31/2021. The educational tools used during this implementation (serious games, videos and educational tools) will have been previously constructed by the PrevHPV SC in collaboration with the different target populations (adolescents, parents, school staff - co-construction phase).

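### Section 7.4 does not stop staff who delivered EMM from supervising the pupils' T1 questionnaire, so self-reported intention, attitudes and declared vaccination in groups 1-4 could be biased towards the taught message

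*Protocol*

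**What the plan says.** Section 7.4 describes one procedure for pupils in all 90 municipalities. The questionnaires are online and self-administered, and the setting is stated: "The adolescent questionnaires will be administered in class under the supervision of a teacher or health professional". No teacher or health professional is excluded from that role.

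The lists linking names to inclusion numbers are "kept in a closed envelope in the locked office of the research referent in the establishment, until they are transferred to the classes at T1". At that point "school staff present in class for the T1 questionnaire will be able to remind students of their inclusion number".

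Section 8 describes EMM for Grades 8 and 9. One of its three main tools is "Educational tools and training intended for biology teachers and school nurses", including "development of an interactive course that they can use with students". Health students also take part where possible: "we will call on health students integrated into the SeSa systems, particularly for interventions with students".

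Section 7.2 asks, for the schools of groups 1-4, that "a referent be appointed within each middle school (school nurse/doctor, biology teacher, administrator, etc".) be the study's contact.

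Section 5.1 limits EMM to groups 1-4, while section 7.4 surveys pupils in all six groups. Section 11.3.2(i) analyses the linked T0-T1 change, counting a move from no on both intention and vaccination to yes on either. It also plans a difference-in-difference model with a group-by-after interaction.

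**The concern.** The people equipped to teach the message fall within the two categories of people allowed to supervise the questionnaire that measures its effect. Where the roles coincide, a pupil in an EMM school states intention, attitudes and vaccination status at T1 with the person who taught the topic in the room. Some pupils may then answer as they think is expected.

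In groups 5 and 6 the trial trains no such person, and at T0 the EMM sessions have not yet taken place. The influence would therefore be confined to one time point and one side of the comparison. All pupil outcomes of secondary objective 1 are self-reported. The change outcome counts only positive moves, so a yes given to please would be scored as a success of EMM. No later analysis could separate this from a true effect; it has to be prevented in the field procedure, which section 7.4 already lays down.

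**Working it through.** **1. Can the roles overlap?**
- Supervisor (7.4): any teacher or health professional, in class, Grades 8 and 9.
- EMM staff (8): biology teachers and school nurses, with a course for Grades 8 and 9; health students as well.
- Referent (7.2): may be a nurse or a biology teacher; keeps the lists until T1 (7.4).
- Rule separating the roles: none found.

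The overlap is therefore allowed. How often it would occur is not stated.

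**2. Would the planned models remove a bias?** Let d be the common time trend, τ the true EMM effect and b a shift in reporting at T1 in EMM schools.
- Change in EMM schools: d + τ + b.
- Change in schools without EMM: d.
- Difference in differences: τ + b.

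The baseline cancels and b does not. Linking T0 and T1 by inclusion number leaves the same sum.

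**3. Which comparisons are exposed?** With 15 municipalities per group, section 11.3.2(i) lists:
- (a) EMM or not, among those without the vaccination campaign: groups 2+4 against 5+6, 30 v 30. Exposed.
- (b) campaign plus EMM against neither: groups 1+3 against 5+6, 30 v 30. Exposed.
- (c) GP training or not, among those with EMM: groups 1+2 against 3+4. EMM is on both sides, so the overlap is not differential by design.

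**4. The plan's own figure.** Section 11.2 gives 15 clusters per group. That figure concerns vaccination coverage, not this survey, but it shows how the ICC and CV enter.
- Two proportions, 7.86% v 17.86% (the 10% increase read as percentage points), 90% power, two-sided 5%: 234 per arm.
- Design effect = 1 + ((CV² + 1)m − 1) × ICC = 1 + (1.25 × 466 − 1) × 0.05 = 30.08.
- 234 × 30.08 / 466 = 15.1 clusters. Power with 15 is 89.9%. The figure reproduces.

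**5. Scale for the survey (illustration).** Inputs: ICC 0.05 and CV 0.5, borrowed from section 11.2. Assumed: 233 pupils per municipality (466 / 2, two of four grades, one school, everyone responding) and a percentage answering yes of 30% to 50%.
- Design effect = 1 + (1.25 × 233 − 1) × 0.05 = 15.51.
- Variance of a cluster mean = p(1 − p) × 15.51 / 233 = 0.0140 (p = 0.3) or 0.0166 (p = 0.5).
- SE for 30 v 30 = √(2 × variance / 30) = 3.1 points (p = 0.3) or 3.3 points (p = 0.5).
- A 3-point shift: 3 / 3.3 to 3 / 3.1, about 0.9 to 1.0 SE.
- A 5-point shift: 5 / 3.3 to 5 / 3.1, about 1.5 to 1.6 SE.

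**6. What could produce such a shift?** The document gives no figure. If 40-80% of EMM pupils would truly answer no at T1, and 2-10% of those answered yes because of the supervisor, the percentage of yes would rise by between 0.40 × 0.02 = 0.8 points and 0.80 × 0.10 = 8.0 points. The assumed 3-5 points lie inside that range, which itself rests on assumption alone.

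**The case against.** The strongest reply is that this is a possibility, not a documented defect.

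- **The overlap is partial.** Any teacher may supervise, but only biology teachers and nurses receive the EMM tools. Section 6 says the tools may or may not be used, and health students may lead the sessions. This stands: the frequency is unknown.
- **The answers are protected.** Questionnaires are online, the lists are kept sealed and destroyed after T1, investigators do not see them (7.4), and responses are stored under the number only (10.2). This also stands. A reader might infer that the supervisor can identify a pupil's answers. The documents do not support that: the list links names to numbers, and nothing gives the supervisor the responses. The safeguards protect confidentiality, however; they do not change who is in the room.
- **The list is not specific to EMM schools.** The procedure is the same in all groups, so the list alone cannot create a difference between them.
- **HPV may already be taught elsewhere.** Section 6 says other subjects and sexuality education can cover it, so pupils in groups 5 and 6 may also have met the topic. This could narrow the contrast, but those staff would not have been trained by the trial.
- **Significance is not the decision rule.** Section 11.3.2(i) sets no predefined level, so false-positive rates at 5% are not the right measure here. The bias would act on the estimates and the exact P values.
- **The standard error is rough.** It describes a T1-only contrast, whereas linked change and difference-in-difference analyses are planned. The ICC was set for coverage, and full response is assumed.
- **Higher knowledge scores may simply be the intended effect.** The concern is therefore strongest for intention, attitudes and declared vaccination.

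**Conclusion.** The concern holds as a preventable gap. Section 7.4 allows those who delivered EMM to supervise T1, and any resulting bias would fall only on groups 1-4 after the intervention, where the planned models would read it as an EMM effect.

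A reader might go further and conclude that T1 answers in these groups are in fact pulled towards the message. The documents do not show that. They never say that the same person teaches and supervises, and they give no basis for the direction or size of an effect. On the assumptions above, a shift of 3-5 points would be about 0.9 to 1.6 standard errors of the planned 30 v 30 comparisons: enough to distort an estimate if it occurred.

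The reach is limited to pupils' self-reports under secondary objective 1. The primary outcome comes from reimbursement data, centre data and school vaccination counts (3.1), parents answer at home, and GPs are surveyed separately. This is a cheap improvement to the field procedure and does not threaten the trial's main result.

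**What to change.** In section 7.4 and the instructions to schools, state that:
- in all 90 municipalities, T0 and T1 are supervised by a member of school staff who took no part in EMM or school vaccination, for example a teacher of another subject;
- one common neutral script is used, with no help on answers;
- at T1, inclusion numbers are handed out on individual slips prepared beforehand, so that the list need not be in the room.

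The first two items address the difference between groups. The slips only reduce pupils' sense of being identifiable, and apply equally everywhere. Pupils will still know that their school gave EMM, so some desirability effect may remain.

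The cost is a change of wording and some timetabling effort in small schools. No extra staff are needed.

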A KABP-6C survey, at the individual level, repeated cross-sectionally (pre and post interventions) will make it possible to answer secondary objective 1 of the PrevHPV trial and thus to assess knowledge, attitudes, beliefs and practices. The KABP-6C questionnaire will be administered to volunteers in the following populations:

- Students, girls and boys, enrolled in Grades Eight and Nine in one of the public or private middle schools in the 90 municipalities of groups 1 to 6 before the implementation of the components in middle schools (December 2020) and after (May 2021).
- Parents, fathers and mothers of girls and/or boys enrolled in Grades Six through Nine in one of the public or private middle schools in the 90 municipalities of groups 1 to 6 before the implementation of the middle school components (December 2020) and after (May 2021).
- GPs practicing regular consultations with adolescents in the 60 municipalities of groups 1, 2, 5 and 6 before the implementation of the component (December 2020) and after (April 2021).

Costs and implementation indicators are collected prospectively by the referent of each middle school with the help of the PrevHPV project manager of the geographical sector concerned, as the different components of the intervention are implemented.

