### **11.3.2. Analysis of secondary outcomes**

#### **(i) Analysis of secondary objective 1**

For the analysis of this objective, people with a positive change in intention/vaccination will be identified (change from “no” for both at T0 to “yes” for one of the two at T1).

The variables corresponding to the KABP-6C items will be created in particular by calculating knowledge scores and Likert scale medians.

For an analysis of T0, the percentages and medians of the items will be presented by intervention group, namely:

- a. By EMM groups 0 and 1, among participants without vaccination campaign, without taking into account the GP intervention
- b. By school interventions (campaign + EMM vs. without campaign or EMM), without taking into account the GP intervention
- c. By GP groups 0 and 1, among participants with EMM, without taking into account the vaccination campaign intervention

For an analysis of the main effects, the percentages of people with change and the medians of the differences will be presented by group (see a., b., and c.).

The differences will be tested first by suitable non-parametric tests (Fisher's and Wilcoxon, ranksum).

Multilevel models with a binary or continuous (linear) dependent variable will then be constructed in order to estimate the effect of interventions alone or in interaction, while taking into account intraclass correlation effects (cluster randomization). The interactions to be studied as a priority are:

- between the GP intervention and the school intervention (EMM+campaign),

- between the vaccination campaign intervention and the GP intervention (only possible in combination with EMM)
- between the EMM intervention and the GP intervention (only possible in the absence of a vaccination campaign)

For an analysis not taking into account individual evolution between T0 and T1, the effect of each intervention (alone or in interaction) will be estimated from a difference-in-difference model, i.e. including an interaction between the intervention group (among the 6 defined, with the control group as reference) and the temporal indicator “after” (vs. before) intervention.

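### The T0–T1 link for parents in the KABP-6C survey rests on the child's number, which has no described route to parents with children only in Grades 6–7 and does not separate two parents of one child

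*Protocol*

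**What the plan says.** The KABP-6C survey has different grade limits for pupils and parents. Protocol section 4.2 includes "Students, girls and boys, enrolled in Grades Eight and Nine", but for parents it includes "Parents, fathers and mothers of girls and/or boys enrolled in Grades Six through Nine". Section 7.4 repeats the Grade 8–9 limit for pupils and sets no grade limit for parents.

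On numbering, section 7.4 says: "Each participant will be assigned an inclusion number, determined in advance by the middle school referent". This stands in the paragraph on adolescent questionnaires completed in class. Pupils copy the number into their correspondence notebook at the T0 session, and a list is made for each class so that staff can remind pupils of it at T1. For parents the instruction is: "Parents will be asked to enter their child's inclusion number (given in class and noted in the correspondence book"). They are asked to keep that number for T1.

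Section 7.4 gives this one number two tasks. It describes the "inclusion number (which will make it possible to establish the link between T0 and T1, and between children and parents"), and says the match to identity exists only in the notebook and on the class list. Each participating GP, by contrast, receives a number of his or her own.

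Section 10.2 stores the answers with the inclusion number and no other identifying information. In section 11.3.2 (i), the analysis of secondary objective 1 begins with individual change: "people with a positive change in intention/vaccination will be identified", meaning no at T0 for both intention and vaccination, then yes for either at T1. It also plans a difference-in-difference model that does not follow individuals.

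**The concern.** The parent frame spans four grades, while the linking key is handed out in two. A family whose children are all in Grades 6–7 is invited to both questionnaires and asked for a number it has no stated way to obtain. The individual-change analysis would then rest on families with a Grade 8–9 pupil. In the EMM arms those are the families whose children are taught directly (sections 4.3 and 8). Parents of Grade 6–7 pupils are also EMM targets, and in groups 1 and 3 their children may be vaccinated at school (section 5.2). The linked result would therefore describe a narrower population than the one stated.

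The number also belongs to the child. A mother at T0 and a father at T1 would enter the same key, and a parent with two pupils in the school could hold two keys. Section 3.2.1 measures intention to vaccinate the respondent's child, and no rule fixes which parent answers or for which child.

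This is a matter of data collection. If T0 runs without numbers for these families, or without a record of who answered, no later analysis plan can rebuild the pairs.

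**Working it through.** The protocol gives no figure for linkage, so there is none to reproduce. The check compares the sections and then sizes the gap.

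**Step 1: who is surveyed and who receives a number (sections 4.2 and 7.4)**

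| | Grades 6–7 | Grades 8–9 |
|---|---|---|
| Parents surveyed | yes | yes |
| Pupils take the in-class T0 survey | no | yes |
| Described route of the number to the family | none | class session, then notebook |
| Number belonging to the parent | none | none |

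**Step 2: share of parents without a route**

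Let *g* be the share of responding parents whose surveyed child is in Grade 6–7, and *s* the share of those who also have a child in Grade 8–9 and so could use that child's number. The share without a route is *g* × (1 − *s*). The protocol gives neither input, so both are assumptions.

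- Base case (four equal grades, equal response, no older sibling): *g* = 2/4 = 0.50, *s* = 0, giving 0.50 × 1 = 50%.
- *g* = 0.50 with *s* = 0.10, 0.20, 0.30: 45%, 40%, 35%.
- Lowest corner: *g* = 0.40, *s* = 0.30, giving 0.40 × 0.70 = 28%.
- Highest corner: *g* = 0.60, *s* = 0, giving 60%.

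For scale, section 11.2 expects 90 × 466 = 41,940 adolescents with one school per municipality. With four equal grades, 41,940 × 2/4 = 20,970 would be in Grades 6–7. This counts pupils in the frame, not responding parents.

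**Step 3: two parents, one key**

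If pairs are formed on the number alone, the share of linked pairs that mix mother and father equals the share of linked households in which a different parent answers at T1. The protocol gives no value for it, and it can be zero.

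**Step 4: which analyses need the link**

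- Individual no-to-yes change and medians of individual differences (section 11.3.2 (i)): link needed.
- Difference-in-difference model (same section): not needed.
- Parent outcomes in the section 3.2.1 table, which are before-after changes in percentages or medians: not needed as defined.
- Primary outcome, analysed by municipality (section 11.3.1), and the sample size: unaffected.

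**The case against.** **The gap is inferred from silence.** The referent sets numbers in advance for each participant, lists are made by class, and invitations go through the school's usual channels. Numbering Grade 6–7 classes is not excluded, so a reader who infers that these parents will never receive a number goes further than the text. What stands is narrower. The sentence belongs to the paragraph on in-class questionnaires, the lists serve classes that sit the T1 questionnaire, and even on the generous reading no delivery to Grade 6–7 parents is described. The same caution applies to a Grade 8–9 pupil absent at T0, who may already have a number on the class list.

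**The questionnaire may already separate the parents.** Section 10.1 says individual characteristics are collected, and the questionnaire appendix is not shown. If sex or relationship to the child is an item, number plus item may resolve most cases. A reader might infer that some pairs certainly compare two different people. The documents support only a risk.

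**The harm may be small.** Sections 4.2 and 7.4 call the survey repeated cross-sectional, the tabulated parent outcomes are group-level, and an unlinked model is planned. All of this stands and limits the point to one analysis. It does not remove the point, because that analysis is the first one described for secondary objective 1.

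**Spurious conversions cannot be sized from the documents.** A reader might calculate false no-to-yes changes as mixed share × p(1 − p) × (1 − kappa). With 20% mixed pairs, p = 0.50 and kappa = 0.5 this gives 0.20 × 0.25 × 0.5 = 2.5 points. None of these inputs is in the protocol, and the result is zero if nobody switches. If switching is alike across arms, the false changes largely cancel between arms. The figure should not be used as an estimate.

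**Conclusion.** The point holds in a limited form. The procedure in section 7.4 does not secure the T0–T1 link for parents. It describes no route to the number for parents with children only in Grades 6–7, and the key does not distinguish two parents of one child.

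About half of surveyed parents would be unlinkable under equal grades, equal response and no older sibling. The share is roughly 28–60% when *g* runs from 0.40 to 0.60 and *s* from 0 to 0.30. Even the low end is material for a linked analysis. Attrition between T0 and T1 comes on top and is not counted. Mixed-parent pairs are a possibility of unknown frequency, dependent on questionnaire items that cannot be seen here.

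The consequence is a linked parent sample that may represent only families with a Grade 8–9 pupil. It should be corrected because the loss cannot be repaired after T0 and the correction is cheap. It does not threaten the trial's main conclusion.

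**What to change.** In section 7.4:

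1. Have the referent prepare inclusion numbers for all pupils in Grades 6 to 9, and send them to families with the letter already planned in section 7.3 or with the survey invitation.
2. At T0 and T1, record the respondent's role (mother, father, other guardian) and one index child, if the questionnaire does not already do so. A parent with several pupils answers for the same child both times.
3. Form a T0–T1 pair only when number and role both match. Keep unmatched parents in the unlinked difference-in-difference model.
4. If numbers are not extended to Grades 6–7, state that the linked parent analysis represents only parents of Grade 8–9 pupils.

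Two existing commitments need checking. Section 10.1 promises to avoid indirectly identifying variables, so the new fields should stay coarse. Section 7.4 limits where the number-to-identity match is kept and destroys class lists after the T1 class session, so it needs a storage and destruction rule for Grade 6–7 lists.

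The cost is number lists for two more grades per school, one or two questionnaire fields, and a few sentences of protocol text.
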